**Discussion**

About 1-1.25 million patients undergo cardiac surgery worldwide each year and the number continues to increase [40]. CPB is an essential part of major cardiac surgery which may induce PPCs after operation. Since the PPCs are leading causes of mortality and morbidity [37], the effective preventive measures are particularly important and urgently needed. Various researches have been performed to reach this goal. The MECANO trial (NCT03098524) aims to assess the effects of mechanical ventilation (V_T_: 3ml/kg, PEEP: 5cmH_2_O, RR: 5bpm) on all-cause mortality and respiratory failure comparing with no ventilation during CPB [41]. It does not provide the detailed usage of oxygen though the ambitious number of patients (n=1500). The CPBVENT trial (NCT02090205) is a three-armed multicenter study [42], which compares two different ventilation strategies (CPAP: 5cmH_2_O or V_T_: 2-3ml/kg of IBW, PEEP: 3-5cmH_2_O, RR: 5bpm) with no ventilation during CPB. This trial’s primary endpoint (PaO_2_/FiO_2_ ratio) can be easily identified, observed, and calculated, but indirect. That is why we use it as a secondary endpoint. Besides, the inclusion and exclusion criteria are relatively strict, making the conclusion only applicable to a specific group of populations. The purpose of the VONTCPB study is to determine the impact that the different FiO_2_ has on the PPCs when combining the ventilation strategy with low V_T_（3-4ml/kg of IBW, only about half of the normal tidal volume）, routine respiratory rate (10-12 bpm) and PEEP (5-8 cmH_2_O) during CPB. This trial is the first study to investigate the effect of oxygen under different ventilation strategy during CPB. The number of the sample size (n=420) is adequate. The primary endpoints are clinically relevant. The purpose of setting ventilator parameters in this way is to make the ventilation closer to the general. And this ventilation management during CPB may potentially benefit patients’ outcomes, but at the same time it has an imperceptible impact on the operating field.

There are limitations of the trial due to the inherent properties such as its single-center design. It is questionable whether the conclusion drawn by the VONTCPB trial can be applied in other hospitals because of the different clinical practice in other hospitals. Besides, only the volume controlled ventilation mode is applied, so it is unknown whether it is also applicable in other ventilation mode, such as pressure controlled mode.

In general, the VONTCPB trial would answer the question that whether maintaining mechanical ventilation during CPB is more preferable than no ventilation. Better still, which level of FiO_2_ is beneficial to patients will be determined from this trial.

**Abbreviations**

ASA: American Society of Anesthesiologists; ACT: activated clotting time; ABG: arterial blood gas; ARM: alveolar recruitment maneuver; BIS: bispectral index; CPB: cardiopulmonary bypass; CPAP: continuous positive airway pressure; CRF: case report form; ECG: electrocardiogram; FiO_2_: inhaled oxygen concentration; IBW: ideal body weight; ICU: intensive care unit; PPCs: postoperative pulmonary complications; PEEP： positive end-expiratory pressure; PaCO_2_: partial pressure of carbon dioxide; PaO_2_: arterial blood partial pressure of oxygen; P_ET_CO_2_: end-tidal carbon dioxide partial pressure; RR: respiratory rate; RCTs: randomized controlled trials; SpO_2_: pulse oxygen saturation; SvO_2_: mixed venous oxygen saturation; SIMV: synchronized intermittent mandatory ventilation; TEE: transesophageal echocardiogram; V_T_: tidal volume.

**Declarations**

**Ethical Approval and Consent to participate**

This clinical study protocol has been approved by the West China Hospital of Sichuan University Biomedical Research Ethics Committee on 12 March 2018 (Approval number 2017 （400）). We will obtain informed consent from patients when recruiting before the experiment. The patients can withdraw from the trial at any time.

**Consent for publication**

All authors agree to its submission to ***Trials*** and publish it.

**Availability of supporting data**

Not applicable.

**Competing interests**

The authors declare that they have no competing interests.

**Funding**

Not applicable.

**Acknowledgements**

Not applicable.

**Authors’ information**

See the title page.

**Additional file**

Additional file 1: The SPIRIT 2013 checklist of this trial.

**Figure legends**

**Figure 1.** Flow diagram of allocation, intervention, data collection and follow-up.

**Figure 2.** Flow chart. Abbreviations: CPB: cardiopulmonary bypass, TV: tidal volume, IBW: ideal body weight, PEEP: positive end-expiratory pressure, RR: respiratory rate, FiO_2_: inspired oxygen fraction, SIMV: synchronized intermittent mandatory ventilation, SAE: severe adverse effect.

**Figure 3.** SBT: spontaneous breathing test; HFNC: high-flow nasal oxygen cannula; NIV: non-invasive ventilation.

***
[figure not shown]
***

[figure not shown]

***Figure 3.*** Simplified protocol of weaning from invasive mechanical ventilation

***
[figure not shown]
***

***Table 1.*** Definitions of post-operative pulmonary complications*

| Complication | Definition |
| --- | --- |
| Respiratory failure | At least one of the following criteria after surgery:   - SpO_2_ ＜90% and requiring oxygen therapy - PaO_2_/FiO_2_ ＜300 - PaO_2_ ＜60 mmHg |
| Respiratory infection | Postoperative antibiotic therapy administered for suspected respiratory infection with at least one of the following criteria:   - New or changed sputum - New or changed lung opacity on x-ray - Fever - Leukocyte count ＞12,000/mL |
| Pleural effusion | Evidence at chest x-ray of:   - Blunting of the costophrenic sinus - In upright position: loss of the sharp silhouette of the ipsilateral hemidiaphragm - In supine position: hazy opacity in 1 hemithorax with preserved vascular shadows - Displacement of adjacent anatomic structures |
| Atelectasis | Evidence at chest x-ray of:   - New parenchymal opacification - Shift of the median structures (mediastinum, hilum or hemidiaphragm) toward the affected area - Compensatory overinflation of contralateral lung |
| Aspiration pneumonitis | Inhalation of gastric content in the perioperative period with subsequent acute lung injury |
| Broncho spasm | New expiratory wheezing responsive to treatment with bronchodilators |
| Pneumothorax | At chest x-ray, presence of air within pleural space, with no vascular bed surrounding the visceral pleura |

*Adapted from Bignami et al (2).

***Table 2***. Postoperative pulmonary complications score

| Grade | Definition |
| --- | --- |
| Grade 1 | - Cough, dry  - Microatelectasis: abnormal lung findings and temperature > 37.5°C without other documented cause; normal chest radiograph  - Dyspnea, not due to other documented cause |
| Grade 2 | - Cough, productive, not due to other documented cause  - Bronchospasm: new wheezing or pre-existent wheezing resulting in a change in therapy  - Hypoxemia (SpO_2_ ≤ 90%) at room air  - Atelectasis: gross radiological confirmation (concordance of 2 independent experts) plus either temperature > 37.5°C or abnormal lung findings  - Hypercarbia (PaCO_2_ > 50 mmHg), requiring treatment |
| Grade 3 | - Pleural effusion, resulting in thoracentesis  - Pneumonia: radiological evidence (concordance of 2 independent experts) plus clinical symptoms (two of the following: leucocytosis or leucopenia, abnormal temperature, purulent secretions), plus either a pathological organism (by Gram stain or culture), or a required change in antibiotics  - Pneumothorax  - Noninvasive ventilation, strictly applied to those with all of the following: a) oxygen saturation (SpO_2_) lower than 92% under supplemental oxygen; b) need of supplemental oxygen >5 L/min; and RR ≥ 30 bpm  - Re-intubation postoperative or intubation, period of ventilator dependence (non-invasive or invasive ventilation) ≤ 48 hours |
| Grade 4 | - Ventilatory failure: postoperative ventilator dependence exceeding 48 hours, or reintubation with subsequent period of ventilator dependence exceeding 48 hours |
| Grade 5 | - Death before hospital discharge |

***Table 3***. Extubation criteria evaluation items

| *Evaluation of patients' cough ability*  *1. Subjective assessment*  *Grade 0: no cough reaction;*  *Grade 1: cough is present, but no obvious cough sound or cough velocity*  *Grade 2: strong cough, can hear the sound of cough airflow, but can’t cough sputum out of the artificial airway;*  *Grade 3: intense cough with sputum spurting out of the artificial airway.*  *2. Objective evaluation*  *Objective assessment was mainly achieved by measuring cough peak flow rate (CPF). CPF is an important index to predict the success rate of extubation. CPF is divided into active cough peak flow rate and non-passive cough peak flow rate.*  *Operation method: CPF meter is the first choice, that is, disconnect the ventilator and connect cough peak flow meter to measure; If not, the ventilator was used for measurement (first, the ventilator mode was changed to spontaneous breathing mode (PSV mode), PS was adjusted to 5cmH_2_O, PEEP was adjusted to 3-5 cmH_2_O, and the ventilator waveform was adjusted to flow rate time curve). The patient was asked to cough forcefully after deep inspirations, and the maximum expiratory flow rate of the patient was observed and measured, which was the peak active cough flow rate. If the patient could not complete the cough, the patient was passively stimulated (2ml of normal saline could be dropped into the airway) to cough, and then the maximum expiratory flow rate of the patient was observed and measured, which was the peak flow rate of passive cough.*  *3. The evaluation criteria of good cough ability:*  *Subjective evaluation reached grade 2-3, and objective evaluation of CPF rate ≥60L/min.* |
| --- |
| *Evaluation of the amount of tracheal bronchial secretions*  *1. The amount of sputum can be divided into four levels*  *No sputum: aspirate sputum every 4-6 hours*  *Small amount: aspirate sputum every 3-4 hours, 1 round/time*  *Medium amount: aspirate sputum every 2-3 hours, ≥2 rounds/time*  *Massive: Need to aspirate sputum every hour or less*  *2. Evaluation criteria for less secretion:*  *"Small amount" or "no sputum"* |
| *Evaluation of hemodynamic stability*  *Heart rate≤140 bpm and systolic blood pressure between 90 and 160mmHg without or at low doses of vasoactive drugs.* |
| *Adequate evaluation of oxygenation function*  *FiO_2_≤50%, PEEP≤8cmH_2_O, PaO_2_/FiO_2_≥150 mmHg* |
| *Adequate evaluation of lung function*  *Respiratory rate (RR) ≤35 bpm, maximum inspiratory pressure≤-20 to -25cmH_2_O, tidal volume (V_T_) :5mL/kg, vital capacity≥10mL/kg. No significant respiratory acidosis* |
| *Evaluation of functional stability of nervous system*  *No obvious intracranial hypertension; No new intracranial lesions; GCS score≥8* |

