**Endpoints**

The primary endpoints are the incidence of a composite of PPCs and the PPCs score during hospital stay [35-37]. The detailed definitions of PPCs are shown in ***Table 1***. The score is presented in ***Table 2***. Secondary endpoints are listed as follows: the incidence of oxygen index <300 mmHg at three time points (the moment arriving in the ICU, 6 and 12 hours after arrival in the ICU), the surgical incision healing grade, the intubation time, the length of ICU stay and hospital stay, and postoperative 30-day mortality rate.

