**Data collection**

All the related data are collected on the CRF. Preoperative data include age, height, weight, EuroSCORE Ⅱ, smoking status, diabetes mellitus, peripheral arterial disease, pulmonary comorbidity, pulmonary infection in the past 30 days and the classification of American Society of Anesthesiologists (ASA). Intraoperative data include type and duration of surgery procedure, duration of CPB and aortic cross clamp, units of allogeneic red blood cell transfusions, volume and type of fluids administered. Postoperative data include time to extubation, need for non-invasive ventilator, re-intubation, postoperative hospital stay, temperature, leukocyte count and chest X-ray. Other data at three time points (the moment arriving in the ICU, 6 and 12 hours after arrival in the ICU) include PaO_2_, FiO_2_, and partial pressure of carbon dioxide (PaCO_2_). PPCs events are traced throughout the hospitalization.

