**Statistical considerations**

**Sample size**

Sample-size calculation is based on two-sided alpha error of 0.05 and 80% power. We performed a pilot-study, showing that the P_max_ is 40% in the LOV group (15 patients) and the P_min_ is 22% in the NoV group (14 patients). Therefore, we expect a reduction of 45% in the incidence of this parameter, and then calculate the sample size of 127 patients per group (381 in total). Considering a dropout fraction of 10%, we will finally need a total of 420 participants.

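### The leukocyte threshold in the primary composite is printed per mL, 1,000 times lower than a per-µL limit, so any measured adult count meets it

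*Protocol*

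**What the plan says.** The Protocol's Endpoints section states: "The primary endpoints are the incidence of a composite of PPCs and the PPCs score during hospital stay". For the composite, it refers the reader to Table 1: "The detailed definitions of PPCs are shown in" that table.

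The respiratory infection row of Table 1 has a gate and a list. The gate is: "Postoperative antibiotic therapy administered for suspected respiratory infection with at least one of the following criteria". The list has four items: a sputum change, a lung opacity on x-ray, fever, and "Leukocyte count ＞12,000/mL".

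The Data collection section includes "temperature, leukocyte count and chest X-ray" among the postoperative data and gives no unit for the count. Table 2, which defines the separate complications score, mentions white cells only in words within its pneumonia definition ("leucocytosis or leucopenia, abnormal temperature, purulent secretions"), with neither a number nor a unit.

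**The concern.** Blood leukocyte counts run to thousands per microlitre, which is millions per millilitre. A limit of 12,000 per millilitre is therefore far below any count a patient is likely to have, and the item cannot separate patients with a raised count from those without.

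The list works on an any-one-of basis, so one item that is always true decides the whole list. The row was evidently built to require some confirmation beyond the clinician's suspicion, and as printed that confirmation is lost. The Objectives section defends the composite as a hard outcome, whereas this component would rest on a prescribing decision. An assessor or programmer who follows the text would also classify some patients differently from a clinician who silently reads the limit in the usual laboratory unit.

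**Working it through.** **Inputs from the Protocol**
- Printed limit: 12,000 per mL (Table 1, respiratory infection).
- Rule: antibiotics for suspected respiratory infection AND at least one of four items (same row).
- Role: Table 1 defines the primary composite (Endpoints).

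**Input assumed.** The Protocol gives no leukocyte values. I take a deliberately wide range, 500 to 30,000 per µL.

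**Step 1: convert the printed limit.** 1 mL = 1,000 µL, so

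12,000 per mL ÷ 1,000 = 12 per µL = 0.012 x 10^9/L.

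**Step 2: compare with a per-µL limit.**

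12,000 per µL x 1,000 = 12,000,000 per mL = 12 x 10^9/L.

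12,000,000 ÷ 12,000 = 1,000.

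The printed limit is 1,000 times lower.

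**Step 3: compare with assumed counts.** Ratio = (count per µL x 1,000) ÷ 12,000.

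| Assumed count per µL | Count per mL | Multiple of printed limit |
|---|---|---|
| 500 | 500,000 | 42 |
| 1,000 | 1,000,000 | 83 |
| 4,000 | 4,000,000 | 333 |
| 10,000 | 10,000,000 | 833 |
| 30,000 | 30,000,000 | 2,500 |

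Even the lowest value, a severe leucopenia, passes, so the conclusion does not depend on the count assumed.

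**Step 4: follow the logic.** Let A be antibiotics for suspected respiratory infection, and S, X, F and L the sputum, x-ray, fever and leukocyte items. The component is A AND (S OR X OR F OR L). If L is true for every measured count, the bracket is true whatever S, X and F are, and the component reduces to A.

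**Step 5: does the planned size depend on this?** The limit does not enter the calculation. A three-group chi-square test with rates 40%, 31% (the midpoint, assumed) and 22%, two-sided alpha 0.05 and 80% power (noncentrality 9.635, 2 degrees of freedom) gives:

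- effect: (0.09² + 0² + 0.09²) ÷ (0.31 x 0.69) = 0.0162 ÷ 0.2139 = 0.0757
- n per group: 9.635 ÷ 0.0757 = about 127, the stated figure.

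The only possible link is through the pilot rates, if pilot events were classified under this definition. The Sample size section does not say how they were classified.

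**The case against.** The strongest objection is that this is a one-character slip that nobody would apply. Any clinician would read the limit per µL, and nothing in the Protocol suggests that the literal value was used. That is likely, and it limits the practical harm. It does not make the printed definition right.

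Second, a µ can turn into an m when a document is converted between formats. No µ appears elsewhere in the Protocol to test this. Other special signs (≥, ≤, °) are intact, and mL is used correctly for tidal volume per kg in Table 3, so a true slip remains quite possible. This point stands as a reason to look at the source file first.

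Third, the effect on the composite is not shown, and this also stands. Respiratory infection is one of seven components. A patient would be reclassified only if given antibiotics for a suspected infection, with a measured count, while having no sputum change, opacity, fever or true leukocytosis, and no other component. The Protocol gives no basis for sizing that group. The intensivist and the data collector are blinded, so there is no evident reason for error to differ between arms. The complications score, the other primary endpoint, does not use this number.

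**Conclusion.** The concern holds. As printed, the leukocyte item is 1,000 times lower than a limit of 12,000 per µL and is met by every patient with a measured count. The respiratory infection component therefore reduces, on its wording, to antibiotics given for a suspected respiratory infection. This is a wrong event-defining threshold in a primary endpoint, and nothing else in the Protocol corrects it.

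The conclusion rests on two things: that the source file also reads mL, and that adult counts lie somewhere in the wide assumed range. The statement that all patients qualify applies to this one item only, not to the component or the composite. The effect on the composite rate is probably modest but cannot be quantified from the Protocol. The correction should be made, though it does not call the design or the stated sample size into question.

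**What to change.** 1. Check the unit in the source file of Table 1.
2. If it reads mL, change the item to a leukocyte count above 12,000/µL (12 x 10^9/L).
3. Check that the case report form and any event-derivation program use the same unit. The form is not in the Protocol and may already be right.
4. Confirm which unit was applied to the pilot events behind the 40% and 22% rates, if they were classified with this definition.

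The cost is one corrected unit and a brief check of the form and the pilot records. No patient's treatment changes, and the unit correction itself does not alter the sample size calculation.

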**Data analysis**

Data will be analyzed following the intention-to-treat principle using SPSS version 22.0 (SPSS, Chicago, IL, USA). Comparisons in the dichotomous variables will be made by the chi-square tests (or Fisher exact tests where numbers are small). Comparisons in the continuous variables will be made by analysis of variance or the nonparametric Kruskal-Wallis H test. Two-sided significance tests will be used throughout. The Results will be presented as n (%), mean (SD), or median (interquartile range). Bonferroni correction will be used when doing post hoc analysis.

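### In-hospital death is the worst grade of the PPC score but not an event in the Table 1 composite, and the durations have no rule for it; the effect is probably small and a supplementary analysis would settle it

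*Protocol*

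**What the plan says.** Endpoints section: "The primary endpoints are the incidence of a composite of PPCs and the PPCs score during hospital stay". For the composite it states that "The detailed definitions of PPCs are shown in" Table 1, and it refers to Table 2 for the score.

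Table 1, titled "Definitions of post-operative pulmonary complications", lists seven pulmonary complications, from respiratory failure to pneumothorax. Death is not among them. Table 2 grades the score from 1 to 5, and Grade 5 is "Death before hospital discharge", with no restriction by cause.

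The secondary endpoints include "the intubation time, the length of ICU stay and hospital stay, and postoperative 30-day mortality rate".

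Data analysis section: analysis is by intention to treat. "Comparisons in the dichotomous variables will be made by the chi-square tests", or by Fisher's exact test where numbers are small. "Comparisons in the continuous variables will be made by analysis of variance or the nonparametric Kruskal-Wallis H test". Neither sentence says how a patient who dies is to be entered.

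**The concern.** Death ends the period in which a complication can be observed, and it ends every stay. Most Table 1 criteria need a postoperative blood gas or oxygen saturation, a chest x-ray, a treatment, or time to develop. A patient who dies in theatre or very soon afterwards may have none of these. Under intention to treat that patient stays in the denominator and, on the Table 1 definition, has no event. The same patient has the worst possible value on the other primary endpoint, over the same hospital stay.

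The durations raise a related problem. An early death gives a short ICU and hospital stay, which ANOVA or Kruskal-Wallis reads as favourable unless told otherwise. If early deaths were unevenly spread over the arms, the composite and the two stays would be shifted towards the arm with more of them.

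**Working it through.** **The plan's own figures.** The Sample size section gives a highest rate of 40% (LOV pilot), a lowest of 22% (NoV pilot), two-sided alpha 0.05, 80% power, 127 per group and 420 in total after dropout.

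- Planned spread: 40 − 22 = 18 points; relative reduction 0.18/0.40 = 45%, as stated.
- Three-group chi-square, 2 degrees of freedom: 80% power needs noncentrality 9.63. With the third rate at the midpoint, 31% (my assumption), the noncentrality per patient per group is (0.09² + 0 + 0.09²)/(0.31 × 0.69) = 0.0162/0.2139 = 0.0757. Then n = 9.63/0.0757 = 127 per group. The stated size reproduces and is not at issue.
- Patients per arm: 420/3 = 140.

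**One early death under each endpoint as written** (no Table 1 event recorded before death):

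| Endpoint | Value for this patient |
|---|---|
| Composite (Table 1), primary | No event |
| PPC score (Table 2), primary | Grade 5, worst |
| ICU stay, hospital stay | Short, if entered as observed |
| Intubation time (collected as time to extubation) | Undefined if the patient dies intubated |
| 30-day mortality | Event, if within 30 days |

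**How many deaths could be affected.** Respiratory failure in Table 1 requires "At least one of the following criteria after surgery", and a PaO2/FiO2 ratio below 300 suffices. At the initial ICU FiO2 of 50% stated under Intervention, that is any PaO2 below 300 × 0.5 = 150 mmHg. Blood gas data are collected at ICU arrival and at 6 and 12 hours, and complications are followed for the whole admission. Most patients who die after reaching the ICU would plausibly have met Table 1 first, which leaves mainly very early deaths.

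**Size in the composite.** The protocol gives no mortality figure. Let x be the share of an arm that dies in hospital without a Table 1 event (assumed).

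- Each 1% is 1.4 patients of 140 and moves that arm's composite by 1 point.
- Illustration: three such deaths in one arm and none in another give 3/140 = 2.1 points. The standard error of a two-arm difference near 31% is √(2 × 0.31 × 0.69/140) = 5.5 points, so the shift is about 0.4 standard errors.
- If x is equal in all arms and deaths are counted as events, n for 80% power becomes 129 (x = 1%), 132 (2%) or 137 (5%). Power at 127 goes from 79.9% to 79.2%, 78.5% and 76.7%.

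**Size in the durations.** Moving three of 140 patients from average to the most favourable rank shifts the probability that a patient in one arm outranks a patient in another by (3/140) × 0.5 = 0.011. Its standard error is √(281/(12 × 140 × 140)) = 0.035.

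**The case against.** The case for leaving the plan alone is substantial.

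- *The two definitions may differ.* The composite counts pulmonary complications; the score grades severity. A pulmonary-only composite is a legitimate choice and fits the stated objective, the incidence of complications. This stands. A reader might infer that the tables contradict each other and that death must be put into the primary composite; the protocol does not support that. Doing so would also redefine a primary endpoint of an approved and registered trial whose sample size rests on pilot rates.
- *Death is not overlooked.* It is the worst grade of one primary endpoint, and 30-day mortality is reported. This stands: an early death can look favourable only in the composite or the stays read alone.
- *The durations.* A reader might infer that all three shorten with death. They need not: a patient who dies after long ventilation has long values, and one who dies intubated has no extubation time. A statistical analysis plan, not available here, may already hold a rule for deaths, so this part is the weaker one.
- *The size is assumed.* Power for a death-inclusive composite would fall to 74.7%, 69.1% or 63.2% if 1%, 2% or 3% of patients died without a Table 1 event in the lowest-rate arm only. Nothing in the protocol suggests that pattern.

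What remains is narrow: as written, the composite records a very early death as no event, and the protocol provides no companion analysis that would show whether this mattered.

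**Conclusion.** The point holds as a modest, inexpensive improvement. The differing treatment of death in the two primary endpoints can be read directly from Tables 1 and 2 and needs no assumption; its size depends wholly on an assumed rate of early deaths without a Table 1 event. At 1% to 2% per arm the composite moves by 1 to 2 points, small against the 18-point planned spread and well within sampling error.

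A reader might go further and conclude that the primary result could point the wrong way. The protocol does not support that: it gives no mortality rate and no reason to expect an imbalance in early deaths, and the broad respiratory failure criterion keeps the affected group small.

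**What to change.** 1. Keep the Table 1 composite as it is. Pre-specify a supplementary analysis of any Table 1 complication or in-hospital death, with the same test, to be read with the primary result.
2. Analyse intubation time, ICU stay and hospital stay by Kruskal-Wallis, with patients who die in hospital sharing the worst rank. This also settles the undefined time to extubation. If a statistical analysis plan already has a rule for deaths in these durations, refer to it instead.
3. Tabulate in-hospital deaths by arm beside these results, showing how many had no Table 1 event.

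No new data are needed, because in-hospital death must already be known to assign Grade 5. The sample size is unaffected, since the primary composite does not change. The cost is a little more analysis work, and a few non-pulmonary deaths will enter the supplementary composite and the rankings.
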